### Mindfulness training

The app-based MT (provided by Headspace®) is 15 min long and guides participants through a combination of breathing exercises focusing on the present moment. Participants allocated to this condition will be requested to sign a data privacy acknowledgement to authorise the company to share information with the study researchers at KCL.

This type of intervention could trigger some anxiety in participants while they focus on the present moment. To minimise this, participants will be introduced to the basics of mindfulness before the intervention. Participants will be given the option to stop at any point during the training should they wish to do so due to any unintended effects of the training.

*Procedure:* Individuals allocated to the MT condition will be given free access to the Headspace® app for eight weeks. Participants will be instructed to download the app to their own mobile phones/electronic tablets and sign in with their newly created account. As a feature of the app, participants will be able to choose a time of day when they wish to receive a notification as a reminder of their daily meditation.

The MT is divided into two stages. The first four weeks focus on mindful eating meditation followed by four weeks focusing on overcoming cravings. Both stages (i.e. mindful eating and overcoming cravings) use a meditation technique called ‘noting’, which is an attempt to recognise those instances when the mind has wandered and identify the source of distraction, let it go and return to the object of focus (e.g. the breath).

Every training session (both lab-based and home sessions) will consist of 15 min of guided meditation. Both stages of the training (i.e. mindful eating and overcoming cravings) are divided into three competency levels: weeks 1–2 are the ‘Learn’ level; weeks 2–3 correspond to the ‘Practice’ level; and weeks 3–4-are for the ‘Master’ level.

### Waiting list

After baseline assessment, participants allocated to the waiting list condition will be asked to wait for eight weeks and, once they have completed the post-assessment after their wait, they can opt to receive the online version (i.e. daily home sessions only) of either ABMT or MT for eight weeks. After eight weeks of online training, participants will be asked to complete an electronic assessment including training adherence, current weight and a measure of eating disorder symptoms, eating habits and general mindfulness. No further data will be collected.

### Measures

#### Screening measures

BMI (kg/m^2^);Eating Disorder Diagnostic Scale (EDDS) [36]: a 22-item questionnaire used to identify the presence of an eating disorder (i.e. AN, BN, BED);Structured clinical interview for DSM-V (SCID) [37]: this measure will be used to assess for any major psychiatric condition;Mindfulness practice: previous experience with mindfulness techniques (i.e. > 20 min, twice or more times per week during the past two months) will be assessed.

#### Within-session measures

Before and after each training session, participants in both conditions will complete a VAS measuring hunger and craving for the specific snack used in each session. VAS scales consist of a 10-cm line and participants are requested to indicate a degree or level of a specific emotion or behavioural urge ranging from ‘not at all’ to ‘severe’. After every lab-based training, participants will be asked to report what they ate or drank (apart from water) in the 2 h before the training.

#### Outcome measures

A range of outcome measures will be included with the aim of determining the most appropriate ones for a larger-scale RCT (based on effect sizes). The metric, timing and method of aggregation specifications for all outcome measures are described in the ‘Analyses’ section of this protocol. They are in accordance with Zarin et al. [38].

Clinical outcomes
Eating behaviour-related measures: BMI will be calculated measuring body weight and height (kg/m^2^) and body composition (primarily body fat percentage) will be assessed using a bioelectrical impedance scale (InBody S10). The Eating Disorder Examination Questionnaire (EDE-Q) [39] assesses specific psychopathology of eating disorders using a 36-item self-report format. The Power of Food Scale (PFS) [40] evaluates the psychological impact of the modern ‘obesogenic’ environment. Dietary Recall over 24 h will be used to assess the quality of participants’ diet. VAS scales will be used to measure hunger and craving. In addition, VAS scales for cue-elicited food cravings will be administered after the Food Challenge Task [41] (short films created from Marks & Spencer’s adverts showing palatable foods). The bogus taste test [42] will measure food consumption of highly palatable food (i.e. crisps, chocolates and soft sweets) after asking participants to rate the food items according to smell, taste and attractiveness for 10 min. The difference in grams before and after the taste test will indicate the total food intake;Mindfulness and mindful eating-related outcomes: the Mindful Eating Questionnaire (MEQ) [43] is a 28-item questionnaire which will be used to assess awareness, distraction, disinhibition of eating and emotional and external eating. The Mindful Awareness and Attention Scale (MAAS) [44] is a 15-item scale to assess core characteristics of mindfulness;Other symptomatology: the Depression, Anxiety and Stress- Scale (DAAS-21) [45] is a 21-item self-report questionnaire which aims to evaluate mood, anxiety and stress levels over the previous week. The 20 items related to state-anxiety of the State and Trait Anxiety Inventory (STAI) [46] questionnaire will be used. VAS scales will also be used to measure current mood, stress and anxiety levels.

Neurocognitive outcomes
The Food Attention Network Task (Food-ANT) will be used to assess three components of attention (i.e. orienting, alerting and executive function) using food (low- and high-calorie) versus non-food pictures (neutral items). This task was designed as reported by Hege et al. [47]. Briefly, trials will include a fixation cross, a cue to indicate where the target would appear, and a picture (i.e. the target). In 70% of the trials, participants will be presented with a single arrow pointing either to the left or the right side of the screen to indicate the position of the target. From these single arrow trials, 70% of the time the target will appear on the side where the arrow points (congruent) and 30% of the time the target will appear on the opposite side of the cue (incongruent).In 15% of the trials, a double arrow will appear indicating equal likelihood of the target appearing on either side of the screen and in the other 15% of the trials, the target will be presented without a cue (i.e. no arrow). In double arrow and no arrow trials, the target will appear equally on each side of the screen.

Reaction times (RTs) will be recorded and the different components of attention will be measured by subtracting RTs as follows:

Alerting: a subtraction of the RTs of double arrow (bidirectional) cue condition from the RT of the no cue condition;Orienting: subtraction of RTs of the congruent directional cue from the RTs of the double arrow;Executive function: subtraction of the RTs of incongruent directional cue from congruent directional cue condition.
b)The visual Probe Task (VP) [22] will be used to assess visuo-spatial attention biases for food cues. Test–retest reliability of eye tracking indices (dwell time bias) and RT indices have recently been reported to be reliable measures of AB to food using this task [48]. During the VP, two pictorial stimuli matched for visual characteristics (i.e. one food and one non-food item) will be presented simultaneously on both sides of a computer screen followed by a dot appearing on either the left or the right side of the screen. Participants will be instructed to press the left or right arrow of the keyboard to indicate where the dot appeared. RTs will be recorded as an indirect measure of attention biases under the rationale that participants will be quicker to react to the dot appearing on the side of the picture they were attending to during the stimulus presentation. In addition, eye movements will be recorded as a direct measure of attention biases. The task will consist of two blocks of 60 trials each (120 trials in total). One block will present high-calorie food pictures against neutral items while the other will present low-calorie food pictures against neutral stimulus. The order of the blocks will be counterbalanced for each participant. The probability of the dot appearing behind the food picture or the neutral stimuli, as well as on the left or right side of the screen, will be equal (i.e. 50% on each side of the screen).c)A modified version of the Food-Choice Task [49] adapted for eating disorders [50] will be used to assess for food preference (i.e. low-calorie vs high-calorie). In the first two blocks of the task, participants will be presented with 43 food pictures (25 low-fat and 18 high-fat). The instructions will be to rate the pictures of food according to tastiness and healthiness, respectively. Ratings will be measured using a 5-point scale: for the healthiness block, ratings will go from ‘unhealthy’ to ‘healthy’, whereas in the tastiness block, the scale will go from ‘bad’ to ‘good’. A food item rated as ‘neutral’ on both scales will be used as a reference food for the third block. During the third block or the ‘choice’ condition, participants will have to choose between their reference food and another food item imagining they would be presented with both options at the end of the study as a snack.

Acceptability and credibility
A set of questions related to acceptability and credibility of the interventions will be provided. These questions will include items like ‘How credible did you find this training?’ and ‘How useful did you find this training?’ Questions related to perceived benefits and drawbacks of the intervention will also be recorded to inform any unintended effects of the trainings.

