**Discussion:**

Findings will inform the feasibility of developing a large-scale RCT that takes into consideration effect sizes for primary outcome measures and the acceptability of the design. The study will also provide preliminary evidence on the clinical efficacy of two different attention trainings for people with obesity and associated underlying mechanisms.

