### Secondary objectives

To determine the best instruments for measuring outcomes in a future trial by examining the quality, completeness and variability in the data.To estimate the treatment effect sizes and standard deviations for outcome measures to inform the sample size calculation for a large-scale RCT.To determine whether patients who are overweight/obese view computer-based attention trainings as acceptable and credible.To obtain information about patients’ willingness to undergo random allocation to ABMT, MT or waiting list for eight weeks.To evaluate the relationship between AB and eating behaviour.To identify AB modification after training and its association with symptom change.To compare eating behaviour and weight change between conditions before and after training.To identify potential additional underlying mechanisms of attention trainings related to reward processing and self-regulatory processing using neurocognitive tasks.

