### Sample size

The sample size of this feasibility study is based on standard suggestions considering 12 participants per arm as reasonable sample size for a feasibility trial mainly because estimates of the standard deviation for normally distributed variables tend to stabilise around this size [34]. Considering a sample size of *n* = 36 and assuming the attrition to follow-up rate is a = 0.25, we strive for a sample size of *n* = 45, i.e. 15 participants per group (using an attrition correction factor of 1/(1-a)).

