#### Clinical and cognitive outcomes

Analyses will follow the intention-to-treat principle. Quality, completeness and variability of the outcome measures will be determined by the use of descriptive statistical analyses and graphical methods. Group differences will be estimated using linear mixed effects regression models, controlling for the baseline level of the outcome and the strata variable used in the randomisation. The aim is not to determine significant group differences but to establish a suitably precise effect size for the primary outcome at the post-treatment assessment. This estimate will be used to guide the sample size of a future efficacy trial.

The size of the treatment effect on each outcome measure will be the difference in mean scores between conditions at post-treatment (eight weeks) and follow-up (12 weeks).

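### Choosing the future RCT's outcomes by observed effect size departs from the stated objective and, at about 12 per arm, leans heavily on sampling error

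*Protocol article*

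**What the plan says.** Four places in the protocol article bear on this.

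- **Outcome measures** gives the reason for collecting many measures: "with the aim of determining the most appropriate ones for a larger-scale RCT (based on effect sizes". That sentence names no other criterion.
- **Secondary objectives**, first item: "To determine the best instruments for measuring outcomes in a future trial by examining the quality, completeness and variability in the data". The next item gives effect sizes a separate job: "To estimate the treatment effect sizes and standard deviations for outcome measures to inform the sample size calculation for a large-scale RCT".
- **Analyses, Clinical and cognitive outcomes** plans a descriptive review on the same criteria as the first objective. It then aims to "establish a suitably precise effect size for the primary outcome at the post-treatment assessment" and adds: "This estimate will be used to guide the sample size of a future efficacy trial". The article names no clinical or cognitive measure as that primary outcome; the primary objective is recruitment, attendance and retention. The abstract speaks of a large-scale RCT that "takes into consideration effect sizes for primary outcome measures".
- **Sample size** rests on "considering 12 participants per arm as reasonable sample size for a feasibility trial", on the ground that standard deviation estimates become stable at about that size. It makes no such claim for estimates of treatment effect.

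**The concern.** The objective judges an instrument by how well it measures: whether it is completed, whether the data are good and how much they vary. The Outcome measures section judges it by how far the groups happened to differ. These rules can pick different measures.

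The second rule suits a small pilot badly. A measure can rank high because it is sensitive or because its error fell in the favourable direction, and with about 12 per arm the error is large. A measure picked because its estimate was high also has an estimate that is too high on average. If that number then feeds the sample-size calculation, the next trial is underpowered and may rest on an insensitive outcome. Informing that trial is the declared purpose of this one, so the selection rule touches its main product.

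**Working it through.** The protocol gives no effect size, between-measure correlation or baseline correlation, so there is no stated figure to reproduce on this point. Those inputs are assumptions and are shown as ranges.

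**Inputs**

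- n = 12 per arm (Sample size). This is slightly generous: 45 randomised with 25% attrition leaves 45 × 0.75 = 33.75, or 11.25 per arm.
- K, the number of candidate scores. Counting the Outcome measures section gives 16 clinical scores: BMI, body fat, EDE-Q, PFS, dietary recall, VAS hunger, VAS craving, cue-elicited craving, taste-test intake, MEQ, MAAS, DASS-21, STAI-state, and VAS mood, stress and anxiety. There are 6 neurocognitive scores: three Food-ANT components, visual probe reaction time, visual probe gaze and food choice. The total is 22. K = 10 stands for a deliberately short list.
- r, baseline–outcome correlation: assumed 0 to 0.7 (the models adjust for baseline).
- ρ, correlation between measures: assumed 0 to 0.5.
- One contrast between two arms.

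**Step 1: precision of one effect.** SE(d) = √[(2/n)(1 − r²)].

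- r = 0: √(2/12) = 0.408; 95% half-width 1.96 × 0.408 = 0.80 SD.
- r = 0.5: √(0.1667 × 0.75) = 0.354; half-width 0.69 SD.
- r = 0.7: √(0.1667 × 0.51) = 0.292; half-width 0.57 SD.

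**Step 2: expected largest favourable effect when every true effect is zero.** For K equally correlated normal estimates this is SE × √(1 − ρ) × m, where m is the expected maximum of K independent standard normals (1.539 for K = 10, 1.766 for 16, 1.910 for 22).

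| K | r=0, ρ=0 | r=0, ρ=0.5 | r=0.5, ρ=0 | r=0.5, ρ=0.5 | r=0.7, ρ=0 | r=0.7, ρ=0.5 |
|---|---|---|---|---|---|---|
| 10 | 0.63 | 0.44 | 0.54 | 0.38 | 0.45 | 0.32 |
| 16 | 0.72 | 0.51 | 0.62 | 0.44 | 0.51 | 0.36 |
| 22 | 0.78 | 0.55 | 0.68 | 0.48 | 0.56 | 0.39 |

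For example, 0.408 × 1 × 1.910 = 0.78 and 0.292 × 0.707 × 1.539 = 0.32. If every true effect were 0.3, the selected estimate would average 0.3 more, about 0.62 to 1.08.

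**Step 3: unequal true effects.** Equal effects make any choice a chance choice, so a fairer test gives one measure a true d of 0.6 and 19 others 0.2. Simulation with 12 per arm and ρ from 0 to 0.7 gives:

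- the best measure has the largest estimate 21% to 46% of the time with r = 0, and 31% to 67% with r = 0.7 (picking blindly: 1/20 = 5%);
- the selected estimate averages 1.09 against a true value of 0.28 for the measure selected (r = 0, ρ = 0), and 0.67 against 0.47 in the most favourable setting (r = 0.7, ρ = 0.7).

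**Step 4: consequence if the selected estimate sizes the next trial.** Two-sample t test, two-sided 5%, 90% power: d = 0.8 needs 34 per arm; d = 0.3 needs 235 per arm. With 34 per arm and a true d of 0.3, power is 23%.

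**The case against.** The strongest reply is that the plan never says the largest effect wins. Outcome measures speaks of appropriate outcomes in the plural, and elsewhere completeness, variability and acceptability are listed as inputs too. Read together, the criteria could be cumulative and the wording merely loose. That stands in part. A reader might infer a rule that promotes the single top-ranked measure; the document does not contain one. But the only criterion attached to the sentence about choosing outcomes is effect size, and favouring larger observed effects biases in the same direction even if several measures are kept.

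A reader might also infer that the future sample size will certainly be inflated. The text does not support that. The Analyses section sizes the next trial on the primary outcome, not on whichever measure came top. The full protocol, which may name that outcome, is not shown, so its absence from the article is no fault in itself. The inflation is conditional.

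Nor is the choice pure chance. Step 3 finds the best measure well above the blind rate, and strong baseline adjustment or highly correlated measures help further. It may also be fair to leave the neurocognitive measures, which serve the mechanism objectives, out of the candidate list. A list of 10 with r = 0.7 and ρ = 0.5 brings the expected maximum under no effect down to about 0.32 SD. This reduces the problem without removing it.

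Finally, no participant and no feasibility result of this trial is affected, and the Analyses section disclaims significance testing. That bears on how serious the point is, not on whether the passages agree.

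**Conclusion.** The point holds as an inconsistency with a statistical cost, and it should be fixed. The Outcome measures section states a selection rule that departs from the first secondary objective and gives effect sizes a role that the objectives do not. At about 12 per arm, a size justified only by the stability of standard deviations, that rule is driven heavily by sampling error. With no true effects, the largest of 10 to 22 scores would average about 0.3 to 0.8 SD, for between-measure correlation 0 to 0.5 and baseline correlation 0 to 0.7. The direction of the bias is secure; its size rests on those assumptions.

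The harm to the next trial (34 per arm planned, 23% power if d is 0.3) follows only if the selected measure's own estimate is used for sizing. The article leaves that possible but does not say it will happen. The point does not impugn this trial's primary feasibility objective.

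**What to change.** 1. **Outcome measures:** replace the parenthesis about effect sizes with the criteria of the first secondary objective (quality, completeness, variability). Clinical relevance could be added, but as a new criterion, since the objective does not contain it. State that the observed effect size does not select the outcome.
2. **Before unblinding:** name the candidate primary clinical outcome and the contrast among the three arms. The Blinding section says the data analyst is blinded, so this is practicable.
3. **Analyses:** report that outcome's effect with its confidence interval, and size the next trial mainly on the pilot SD and a minimally important difference rather than on the observed effect. Step 1 alone would not be enough: even an unselected estimate has a 95% half-width of about 0.80 SD unadjusted. The objective on effect sizes can stay, because the interval still shows whether the important difference is plausible.

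The cost is wording and one early decision; no added data, visits or participants are needed. The sponsor gives up the freedom to promote whichever measure moved most, and must justify a minimally important difference for the next trial.

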### Procedure

#### Screening

For participants recruited from general public spaces, study adverts will include the researcher’s contact details for participants to contact them if they are interested in taking part.

Potential participants from a clinical setting will be identified by their clinical care team and ask for consent to pass their details to the research team. Alternatively, patients will be given an information sheet with the researcher’s contact details and the option to contact them if they wish to.

Interested participants who either approach the researcher or are contacted by researcher will be invited to have a phone call for the researcher to answer any queries they may have. To check for eligibility, participants will be asked questions using the screening measures described above.

#### Baseline assessment

If participants are eligible and wish to take part, they will be sent an information sheet and a consent form. Once the consent form is signed, participants will be asked to attend the Institute of Psychiatry, Psychology and Neuroscience to complete a baseline assessment including all the outcome measures described above in addition to demographic and clinical information including age, gender, ethnicity, education, history of previous and current treatments, diet, and previous and current body weight. To control for hunger levels in the assessment session, participants will be asked to not eat or drink anything (apart from water) during the 2 h before the session. Adherence to this request will be measured by asking participants to list what they ate/drank in the last 2 h before the experiment.

#### Post-treatment assessment

The post-treatment assessment will be conducted after eight training sessions and will include all the measures used in the baseline assessment (apart from demographic information). In addition, to control for confounding variables, participants will be asked to answer a questionnaire about acceptability and credibility of the training as well as involvement in other weight-control intervention (including other research) during the eight weeks of training. A member of the research team will carry out assessment sessions with participants and will check outcome measures for completeness to ensure data quality.

Participants in the ABMT group will be asked to return the tablet after completion of the study.

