**Design:**

Forty-five adults who are either overweight or obese (minimum body mass index of 25 kg/m^2^) will be randomly allocated to receive eight sessions over eight weeks of either computerised ABMT or MT or be on a waiting list. Clinical and cognitive outcomes will be assessed at baseline, post-treatment (8 weeks) and follow-up (12 weeks post-randomisation). These include mood, body composition and attention biases. Credibility and acceptability of the trainings will be assessed using questionnaires, and recruitment and retention rates will be recorded.

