**Fig. 1 Fig1:**
[figure not shown]
*Schematic diagram* of study procedures

**Table 1 Tab1:** Assessment timepoints

	Screen visit	Week 1 pre-assessment	Weeks 1–8	Week 8 post-assessment	Week 12 follow-up
Patient information and informed consent	X				
Data sharing Acknowledgement for Headspace® (when applicable)		X			
Eating Disorder Diagnostic Scale (EDDS)	X				
Structured clinical interview for DSM-V (SCID)	X				
Additional eligibility assessment	X				
Visual analogue scale (VAS) for hunger, craving, mood, stress and anxiety levels		X	X	X	
Eating Disorders Examination Questionnaire (EDEQ)		X		X	
Power of Food scale		X		X	X
Mindful Eating Questionnaire (MEQ)		X		X	X
Mindful Awareness and Attention Scale (MAAS)		X		X	
Depression, Anxiety and Stress Scale (DASS-21)		X		X	
State and Trait Anxiety Inventory (STAI)		X		X	
Weight, height and body composition		X		X	
Experimental tasks (Food-Choice task, Bogus taste test, Food-challenge task)		X		X	
Food-ANT		X		X	
Visual Probe Task		X		X	
ABMT/MT			X		
Acceptability questionnaire				X	
Eating habits, self-report body weight					X
Snack Diary (when applicable)			X		
Demographics		X			
Drink and food adherence		X	X	X	

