### Intervention conditions

Participants assigned to either of the two intervention conditions will be asked to attend the Institute of Psychiatry, Psychology and Neuroscience eight times during an eight-week period (i.e. once/week). In addition, participants will be instructed to complete an Internet-based version of the allocated training every day for eight weeks at home (except for days when they have their weekly lab-based session).

For every lab-based training session, participants from both conditions will be asked to choose between three high-calorie snacks. The chosen snack will be available to them to activate craving and reward/self-regulation cognitions during training. Visual analogue scales (VAS) for hunger and craving for the chosen snack will be assessed before and after the trainings to measure any potential changes. In addition, to minimise variability in hunger and satiety, participants will be requested not to eat or drink anything (apart from water) 2 h before each training. Before this window, they will be advised to have a light meal. To establish compliance, drink and food adherence for each training session will be recorded.

Adherence to home sessions will be monitored via self-report (i.e. a training log) and through an output generated electronically at the time of each training. Other than these data on compliance, no further data from daily trainings will be collected.

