#### Follow-up assessment

Four weeks after the last session (i.e. week 12), participants allocated to either ABMT or MT will be contacted via email and will be asked to complete an online version of the EDE-Q including a question on their current weight, the PFS and the MEQ.

For the waiting-list group, the above questionnaires will be sent to participants at the end of the eight weeks of online training in addition to a question related to training adherence and involvement in other weight-control programmes. Participants will be compensated with £50 for their time and effort after completion of the study.

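### The post-treatment visit is triggered by sessions in the trained arms and by weeks in the waiting list, and follow-up has two anchors, so assessment timing can come to depend on attendance

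*Protocol article*

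**What the plan says.** **Post-treatment visit.** Under Post-treatment assessment, "The post-treatment assessment will be conducted after eight training sessions". Under Waiting list, participants "will be asked to wait for eight weeks and, once they have completed the post-assessment after their wait", may then choose an online training. One rule counts sessions and the other counts weeks.

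**Follow-up.** The abstract's Design paragraph gives "post-treatment (8 weeks) and follow-up (12 weeks post-randomisation"). The Follow-up assessment section gives "Four weeks after the last session (i.e. week 12), participants allocated to either ABMT or MT" as the participants contacted. For the waiting list, "the above questionnaires will be sent to participants at the end of the eight weeks of online training", and that training begins only after the eight-week wait.

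**Planned schedule.** Under Intervention conditions, trained participants attend "eight times during an eight-week period (i.e. once/week"). Table 1 places the training in weeks 1 to 8 and labels the visit "Week 8 post-assessment" without distinguishing arms.

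**Use in the analysis.** The Analyses section defines the treatment effect on each outcome as the gap between condition means at eight and at 12 weeks. The mixed model adjusts for the baseline value and the randomisation strata. The post-treatment estimate is meant to guide the sample size of the later efficacy trial.

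**The concern.** A visit triggered by session count moves with attendance, which is behaviour after randomisation. A visit triggered by elapsed weeks does not. When one rule governs ABMT and MT and the other governs the waiting list, any slippage in sessions lengthens the time since baseline in the trained arms only. If weight and eating outcomes change with time, part of a trained-versus-waiting-list difference would then reflect timing, and the model as described has no term for elapsed time.

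Slippage is foreseeable: attendance is part of the primary objective, and the Discussion warns that the commitment required could lead to high attrition. There is also a question under intention to treat. Taken literally, a participant who stays in the trial but never reaches eight sessions has no dated post-treatment visit.

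**Working it through.** **Inputs from the article.** Eight sessions, one per week; waiting-list post-assessment at week 8; trained-arm follow-up four weeks after the last session; waiting-list online training of eight weeks after its post-assessment.

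**Assumed inputs.** *g*, the weeks from randomisation to session 1, and *m*, the weeks lost to postponed sessions. The article gives neither. I also treat baseline and randomisation as the same day, because the waiting list's eight weeks are described as following the baseline assessment.

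**Formulas.**
- Session eight = *g* + 7 + *m*
- Trained-arm follow-up = session eight + 4
- Offset at post-treatment, if the visit directly follows session eight = (*g* + 7 + *m*) − 8

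**The article's own figures.** With *g* = 1 and *m* = 0, session eight falls at 1 + 7 + 0 = week 8 and follow-up at 8 + 4 = week 12. Both stated times are reproduced, and the offset from the waiting list is 0.

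**Other scenarios (weeks from randomisation).**

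| *g* | *m* | Session eight | Offset from waiting list | Follow-up |
|---|---|---|---|---|
| 0 | 0 | 7 | −1 | 11 |
| 0 | 1 | 8 | 0 | 12 |
| 0 | 2 | 9 | +1 | 13 |
| 0 | 3 | 10 | +2 | 14 |
| 1 | 0 | 8 | 0 | 12 |
| 1 | 1 | 9 | +1 | 13 |
| 1 | 2 | 10 | +2 | 14 |
| 1 | 3 | 11 | +3 | 15 |

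The scenario offsets run from one week early to three weeks late. Two rows other than the first and the late ones give exactly zero: *g* = 0 with one postponement, and *g* = 1 with none.

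**Waiting list after week 8.** Post-assessment at week 8 plus eight weeks of online training gives 8 + 8 = week 16 at the earliest. That is 16 − 12 = 4 weeks after the nominal follow-up, and after training of the participant's own choice. This result does not depend on *g* or *m*.

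**The case against.** The strongest reply is that the article ties sessions to the calendar. Eight visits are to fit within eight weeks, Table 1 has one week-8 column for all arms, and the Analyses section calls post-treatment eight weeks. Saying that the visit comes after eight sessions may set an order and not a date: a visit on day 56 does come after a session on day 49. Table 1 also numbers weeks from a week-1 baseline, so a last session on day 49 is in week 8 and day 77 is in week 12, which agrees with "Four weeks after the last session (i.e. week 12"). Visit windows and rescheduling rules commonly sit in the full protocol, and their absence from an article is no finding.

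Most of this stands. A reader might infer that the arms are compared at different times by design, or that trained participants are followed for some stated percentage longer. The documents support neither: the rules coincide on the planned schedule, and every delay in the table above rests on assumed values. Nor do the two anchors for week 12 separate ABMT from MT by design, since one rule covers both.

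What the reply does not remove is that the rules which are printed name different triggering events. Once attendance departs from plan, the text does not say which one governs. It also leaves untouched the missing week-12 measurement in the waiting list.

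**Conclusion.** The point holds in a limited form. The triggers for the post-treatment visit differ between the trained arms and the waiting list, and follow-up is anchored to randomisation in one place and to the last session in another. They nominally agree at weeks 8 and 12. They can part when sessions start late or slip, and the trained arms would then be assessed later than the waiting list by an attendance-dependent amount. Its size cannot be stated from the article; the one to three weeks shown are illustrations under *g* = 1 and *m* = 1 to 3.

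The definite mismatch is at follow-up. The Analyses section compares conditions at 12 weeks, while the waiting list has no assessment then and is next measured at about week 16 following optional training.

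The primary objective, feasibility, is little affected. The consequence falls on the post-treatment effect size intended for planning the next trial, and on any 12-week contrast that includes the waiting list.

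**What to change.** - Date the post-treatment assessment at 8 weeks from randomisation in all three arms, whatever the number of sessions attended. This also gives non-completers who remain in the trial a dated visit.
- Date the follow-up at 12 weeks from randomisation in ABMT and MT.
- Replace the session-count wording under Post-treatment assessment and the last-session wording under Follow-up assessment to match.
- Record the actual date of every assessment.
- In the Analyses section, limit the 12-week between-condition comparison to ABMT versus MT. Adding a week-12 waiting-list visit would not help: those who opted in would be midway through self-chosen training, so it would not give an untreated comparison.

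The cost is protocol wording and date recording. The real downside is that some trained participants will be assessed before their eighth session, so the estimate describes outcome at eight weeks under the attendance achieved and not outcome after a completed course.
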